## Abstract

**Background and aims:**

Tobacco use has posed a tremendous public health problem for China. The Chinese government has taken great efforts to curb the tobacco epidemic. However, the existing smoking cessation services available in China are underused and have some limitations. Our research team intends to develop a smartphone smoking cessation application (SSC APP) and integrate it with the existing smoking cessation services. This study aims to assess the efficacy of the SSC APP developed by our research team through a randomized controlled trial (RCT).

**Methods:**

Current smokers who are motivated to quit within 1 month (n = 1000) will be recruited both online and offline, and all potential participants will register and complete the prescreening assessment online. Participants will be randomly assigned to either the intervention group (receiving the SSC APP and a self-help smoking cessation manual) or the control group (receiving a self-help smoking cessation manual only) using a block randomization method. This study will be a two-arm, single-blind, parallel-group RCT. Participants will be followed up after enrollment through online questionnaires or by phone call. The primary outcome is self-reported 6-month continuous abstinence. The main secondary outcomes include self-reported 7-day point-prevalence abstinence at each follow-up; self-reported 3-month continuous abstinence; reduction in the number of cigarettes smoked per day; and the number of recent quit attempts.

**Discussion:**

If this SSC APP proves to be effective, it could be integrated with the existing smoking cessation services and further facilitate smoking cessation at the population level in China.

**Trial registration:**

Chinese Clinical Trial Registry: ChiCTR2200062097, Registered July 22, 2022.

## Introduction

 Smoking is the single largest preventable cause of disease, disability, and death facing the world. In 2019, tobacco use accounted for 7.69 million deaths and 200 million disability-adjusted life-years loss worldwide [1]. China has approximately 308 million smokers [2], and 2.4 million people in China are dying of tobacco-induced diseases annually [1]. To curb the epidemic of tobacco in China, the Chinese government signed the World Health Organization Framework Convention on Tobacco Control (WHO FCTC), which suggests offering help to quit tobacco use. Besides, in 2019, the State Council issued the ‘Healthy China Action (2019–2030)’, in which the ‘Tobacco Control Action’ clearly stipulated the goal of “reducing the smoking rate of people over 15 years old to 20% by 2030” [3].

Numerous efforts have commenced for tobacco control purposes, one of which is the offering of professional smoking cessation aids. In China, smoking cessation services consist of brief smoking cessation interventions, smoking cessation clinics, and smoking cessation hotlines. Health professionals are suggested to perform brief smoking cessation interventions when smokers visit the hospital [4]. From 2010 to 2018, the proportion of smokers receiving advice from clinicians to quit smoking rose from 33.9 to 46.4% [5]. Besides, since 2014, the Chinese government has started to support the establishment of three Smoking cessation clinics (SCCs) in each province per year [6], as of 2021, China had more than 600 smoking cessation clinics providing professional cessation services for smokers [7]. SCCs generally are located within hospitals, and smokers could visit SCCs for intensive smoking cessation behavior intervention and drug treatment [8]. Smokers in China could also seek cessation services through smoking cessation hotlines, which provide theory-based telephone counseling and behavioral intervention. There are numerous regional and national quitlines offering voice consultation service and manual consultation for smokers in China.

However, these smoking cessation services are underused, with nearly 90% of smokers who have tried quitting over the past 12 months did not seek professional help [5]. Quitting smoking without professional help is hard to achieve as nicotine dependence is a stubborn addictive disease. Previous study indicates only 2-5% of untreated smokers can maintain long-term abstinence [9]. Fortunately, much can be done now. With the advent of internet technology, mobile health (mHealth) has been gradually deployed in the medical field. mHealth is a general term for the use of mobile phones and other wireless technology in medical care. The most common application of mHealth is the use of mobile devices to educate consumers about preventive healthcare services [10, 11]. Many research groups have dedicated themselves to exploiting this to facilitate smoking cessation [12–15], among which smartphone smoking cessation application (hereafter refers to ‘SSC APP’) is one hotspot as SSC APP has the potential to be an accessible, cost-effective, and efficient approach to facilitating smoking cessation and is in line with the development trend of time [16, 17].

Smartphones are rather popular in China, with 986 million people accessing the Internet through their mobile phones [18]. In addition, several studies suggest that Chinese smokers are open to SSC APPs and find it promising [19–22]. Compared with the existing smoking cessation services in China, SSC APP can be accessed at any time, is available anywhere through a smartphone, can reach smokers who want to quit smoking but do not want to seek professional support in person, and can increase the accessibility to evidence-based smoking cessation help. Additionally, we believe the existing smoking cessation services and SSC APP could complement and reinforce each other. Equipping automatic SSC APP with reliable professional health service providers could address smokers’ more specific questions while the deployment of SSC APP may diminish the workload of health professionals in clinics and on quit lines. Overall, there is an opening through which we could simultaneously help more people to quit smoking and optimize the existing smoking cessation services in China.

Due to cultural differences, SSC APPs proved effective in foreign countries may not perform well in China, hence the need to develop SSC APPs based on Chinese culture and relevant context. Several exploratory SSC APPs have been developed in recent years, including two WeChat Mini Programs (a lightweight application that can be accessed and used within the WeChat platform without requiring users to download or install any additional software a portable) developed by Chaoyang Hospital [23] and China-Japan Friendship Hospital [24] and one CBT-based SSC APP developed by Sir Run Run Shaw Hospital [25]. To further advance the development and utilization of SSC APPs, especially personalized ones, the Tobacco Control Office of the Chinese Center for Disease Control and Prevention, which oversees the existing smoking cessation services and is committed to controlling the epidemic of tobacco in China, plans to develop a theory-based, individual-tailored SSC APP and integrate it with the existing smoking cessation services such as smoking cessation clinics to better help smokers quitting smoking. To begin, a randomized controlled trial (RCT) will be conducted to evaluate the efficacy of this SSC APP. The gestation and development of the APP will be detailed in a future paper. This article intends to elaborate on the procedures of the RCT.

## Methods

### Design

This study will be a two-arm, single-blind, parallel-group RCT. It has been registered in the Chinese Clinical Trial Registry (trial registration number: ChiCTR2200062097).

### Study setting

This study will be completely conducted online with no restrictions on setting or location. A WeChat Official Account designed specifically for this study will be deployed to collect the baseline and follow-up data. The recruitment will be conducted from July 2023 to September 2023 or will be terminated when the target sample size is reached. The final 30-week follow-up period is projected to be completed by February 2024.

### Study population

To better understand the efficacy of this SSC APP, our study targets the largest potential user group. Thus, current Chinese smokers who are motivated to make a quit attempt within 1 month will be enrolled in this study.

### Inclusion criteria

Aged 18 or aboveCurrent smoker, including daily smoker and occasional smokerIntend to quit smoking within 1 monthProficiency in smartphoneAgree to take part in this study and is prepared to be assigned randomly to one of two treatment conditionsProvide electronic informed consent

### Exclusion criteria

Currently following other smoking cessation programsHas no access to an Android smartphoneInability to finish the study follow-up

### Sample size and power calculation

The proposed sample size is based on the primary outcome of self-reported 6-month continuous abstinence. Based on a meta-analysis conducted by Ybarra [26], the 6-month continuous abstinence for mobile phone-based smoking cessation intervention is 13.1%, compared with 6.4% in the control group. To detect a 2-sided significant difference between groups with a power of 80% and significance level of 5%, 309 participants in each arm are estimated to be required. Considering a 35.8% loss to follow-up in one study concerning SSC APP conducted in China [27], the final minimum sample size is 481 per group. Eventually, we set a target sample size at 1,000 people to cover the minimum sample size.

### Recruitment and informed consent

Recruitment will take place both online and offline. For online recruitment, Weibo, WeChat Official Accounts, web forums, and so on will be used to post the recruitment advertisements. With respect to offline recruitment, staff in local CDCs will assist in the distribution of recruitment posters and publicity. All recruitment channels will be attached with a Quick Response (QR) code of the WeChat Official Account of this research. After following the Official Account and completing the prescreening assessment, participants’ eligibility will be assessed automatically by computer algorithms. Baseline data, including sociodemographic characteristics and smoking history, will be collected in the prescreening assessment.

Eligible participants will receive a consent form with a summary of this study, including the study procedures, the risks and benefits, the intervention content of both the intervention group and control group, the potential of being allocated to either group, the compensation for participating this study and retaining in follow-up, how confidentiality is maintained, and explaining the data collection and data sharing procedures. Then participants will be asked to provide informed consent electronically by checking the box “I’ve read and understand the content of this study, and I agree to participate in this study.” To prevent unintended checks, a verification code will be required when participants decide to sign the informed consent. Besides, participants will be asked to provide a mobile phone number for short messaging system (SMS) reminders of research progress, follow-up questionnaires, as well as potential follow-up calls if they fail to complete the questionnaires on time.

### Randomization, allocation concealment and blinding

After enrollment, eligible participants will be assigned to either the control group or intervention group in a ratio of 1:1 (500 in each). Two stratification factors, each at two levels, will be used: age (≤ 40 years, > 40) and daily cigarette consumption (≤ 20 pack-years, > 20). A random permuted block sizes of 2, 4, or 6 will be used to achieve similar numbers of participants in both the intervention group and the control group.

Allocation concealment can be guaranteed as the random number sequence will be generated by a biostatistician who is not a member of the research team, and the random number sequence will be kept secret from researchers who are responsible for the recruitment.

As the interventions in two groups cannot be completely blinded in this study, this RCT will be single-blind in which all outcome assessors and data analysts will be blind to group allocation.

### Detailed description of intervention procedure and control group

This study aims to evaluate the efficacy of the individual-tailored smoking cessation intervention APP developed by the Tobacco Control Office. Thus, participants assigned to the intervention group will receive the APP and use it to guide their smoking cessation attempts, while participants in the control group will receive a self-help smoking cessation manual. To balance the effect of the self-help material, participants in the intervention group will receive them as well. In this way, this study could clearly determine the efficacy of this SSC APP.

#### Control group: self-help smoking cessation manual

“To help you stop smoking”, a 24 pages self-help smoking cessation manual developed by the Tobacco Control Office, is comprised of 12 sections, including the harms of smoking, the benefit of quitting smoking, the instruction on quitting smoking and medication usage, how to deal with setbacks, etc.

Participants in the control group will receive the self-help material alone to facilitate their smoking cessation attempts after randomization.

#### Intervention group: individual-tailored smoking cessation intervention APP group

This individual-tailored smoking cessation intervention APP was developed by the Tobacco Control Office. The Behavior Change Wheel (BCW) theory [28, 29] and Transtheoretical Model [30, 31] informed the function development of this APP as the Capability, Opportunity, and Motivation needed to quit smoking at each stage were analyzed thoroughly to justify the functions setting. This APP also embraces the key elements and concepts of cognitive behavioral therapy (CBT), including changing underlying beliefs about smoking and learning and practicing a variety of coping skills [32–34]. Also, during the development of this APP, suggestions and feedbacks from volunteer smokers were seriously considered. When the fundamental framework was formed, the Delphi method was exploited to solicit opinions and effective techniques from experienced smoking cessation experts and refine the APP iteratively. To recapitulate, this APP is theory-based and user-centered.

At the first login, users will receive a thorough assessment questionnaire to evaluate their current stage, quit motivation, past quit attempts, current smoking usage, and conceptions about smoking. This functional analysis could set the stage for later individual-tailored interventions. Then, an assessment report will be generated accordingly, including users’ addiction level, current stage of behavior change, barriers to and facilitators of smoking cessation, personalized advice, and so on. Those in the preparation stage will be suggested to set a quit date and will receive stepwise guidance about the wherewithal to quit smoking. Considering the withdrawal symptoms and other challenges facing current smokers, users will receive tips and aids for coping with withdrawal symptoms, urges to smoke, and other problems during the first month. As for those in the contemplation stage, they may not yet be ready to make a quit attempt, hence they will be prompted to use this APP to record their smoking behavior, which provides an opening through which the APP could further intervene by sending specific motivational messages and presenting other smoking cessation-related material to them. These interventions may catalyze the transition from contemplation to preparation to quit. Along with these interventions and instructions, other functions will also be exploited to facilitate smoking cessation, such as an emergency help when smoking cravings occur. The gamification principle will be deployed to optimize the user experience as well. The functional framework of this SSC APP is shown in Fig. 1.

**Fig. 1 Fig1:**
[figure not shown]
Functional framework of the SSC APP

Participants in the intervention group will receive this APP and the self-help material to facilitate their smoking cessation attempts after randomization.

### Follow-up and data collection

Participants in both groups will be followed up for 6 months and receive electric follow-up questionnaires sent by the WeChat Official Account 1 month, 3 months, and 6 months after enrollment. SMS will be used to remind them to complete the questionnaires on time. Non-responders will receive up to 3 additional reminder messages or calls within 1 week following the initial invitation. Compensation will be paid to improve their willingness to respond and remain in this study. When the follow-up finishes, participants in both groups will be acknowledged for their participation and participants in the control group will be referred to our SSC APP if they have not quit smoking.

### Compensation

Participants in both groups will receive compensation through phone bill recharge after completing each follow-up questionnaire to stimulate their motivation to remain in the study. Considering participants are more likely to drop off at later follow-ups, the compensation will increase successively but the total financial value of the compensation will stand at 50 RMB (approximately US $7.86). Participants from both intervention and control groups will receive the same amount of compensation, and the answers to the questionnaires will not have any impact on the value of compensation received.

### Withdrawal from the program

It will be emphasized in the recruitment advertisement and the informed consent form that participation in this study is voluntary, and that participants will be free to withdraw at any stage of the study.

### Outcomes and measures

#### Primary outcome and measures

As we explained before, our SSC APP includes motivational protocols for those not ready to decide on a target quit date. In this study, we intend to explore the efficacy of the SSC APP as a whole, so the follow-up in this study will be tied to the date of intervention initiation. 6-month continued abstinence is selected as the primary outcomes. Considering there is no close contact or interaction between participants and the study team, biochemical verification may be infeasible as the SRNT guidelines have suggested [35], it will be self-reported. 6-month continued abstinence will be defined using the Russell 6 Standard [36] but without biochemical verification (i.e., tolerate fewer than five incidents of smoking from the quit date) and will be measured through the question “Have you smoked at all since (date of the start of the continuous abstinence period) ? A: No, not a puff; B: 1–5 cigarettes; C: More than 5 cigarettes.”

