#### Secondary outcomes and measures

The following secondary outcome measures will be assessed in all participants at 1-month, 3-months, and 6-months after enrollment: 7-day point-prevalence abstinences, 3-month continuous abstinence, reduction in the number of cigarettes smoked per day, the number of quitting attempts, and attendance to other smoking cessation services.

The 7-day point-prevalence abstinence will be measured through the question “Have you ever smoked over the past 7 days?” The measurement of 3-month continuous abstinence is identical to that of 6-month continued abstinence as explained before. The number of cigarettes smoked per day and the number of quitting attempts will be asked at each follow-up. Attendance to other smoking cessation services will be measured through the question “Have you ever used any other professional smoking cessation services? If yes, please describe them briefly.”

As the participants in this study will be smokers willing to quit within 1 month, we presume this study will mainly reveal if our APP could help smokers in the preparation stage to quit successfully. However, since not every smoker proclaiming interest in quitting will make a quit attempt by their due date [37], this study could also explore whether our APP can increase the motivation of smokers to quit smoking. Therefore, we will specifically measure how many participants in each group have made attempts to quit 1 month after enrollment to explore the efficacy of our APP in increasing the motivation to make a serious quit attempt.

For those who relapse at the follow-up points, the reduction in the number of cigarettes smoked per day, the number of quit attempts, and attendance to other smoking cessation services will be considered as secondary outcomes and will be used to compare against the baseline data.

Furthermore, APP acceptability and engagement will be measured in the intervention group 1 month after enrollment by an adopted TAM (Technology Acceptance Model) questionnaire, which involves perceived usefulness and perceived ease of use [38]. Also, the frequency and duration of each login, the utilization of each specific function, and the compliance with guidance will be recorded automatically for further analysis. The full list of measurements is presented in Table 1.

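### Six months of abstinence counted from a quit date after enrolment cannot be seen at a last questionnaire six months after enrolment, and the start of the abstinence period is not fixed

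*Protocol article*

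**What the plan says.** All references are to the Protocol article.

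- **Endpoint.** Primary outcome and measures states "6-month continued abstinence is selected as the primary outcomes". It adopts the Russell standard without biochemical verification, described as "tolerate fewer than five incidents of smoking from the quit date". The outcome question asks about smoking since the start of the abstinence period, and that date is a placeholder.
- **Clock.** The same section says "the follow-up in this study will be tied to the date of intervention initiation". Follow-up and data collection sends questionnaires to both groups "1 month, 3 months, and 6 months after enrollment", with reminders to non-responders for up to one week. Procedures repeats a 6-month follow-up.
- **Another length.** Study setting refers to "The final 30-week follow-up period", to be completed by February 2024 after recruitment from July to September 2023. No questionnaire at 30 weeks is described.
- **Population.** Inclusion criteria require current smokers, daily or occasional. Study population says "current Chinese smokers who are motivated to make a quit attempt within 1 month will be enrolled in this study". Secondary outcomes and measures expects that some will not attempt to quit by their due date.
- **Quit date.** In the description of the app: "Those in the preparation stage will be suggested to set a quit date". No such step is described for the control arm.
- **3-month abstinence.** The secondary outcomes are to be "assessed in all participants at 1-month, 3-months, and 6-months after enrollment: 7-day point-prevalence abstinences, 3-month continuous abstinence", with the same measurement method as the primary outcome.

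**The concern.** The endpoint needs 6 months after quitting, the schedule gives 6 months after enrolment, and the participants have not yet quit at enrolment. Both candidate starting points then go wrong. If the period runs from each person's quit date, what is measured is shorter than 6 months and varies between people. If it runs from enrolment or intervention initiation, people who quit as the eligibility criterion foresees have usually used up the small smoking allowance before they stop.

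At stake is what the primary result means. The sample size rests on 13.1% versus 6.4%, given for 6-month continuous abstinence. A strict reading of the endpoint would lower both rates and lose power. A loose reading would report a mixture of durations under a 6-month label. If individual quit dates filled the placeholder, the app could also influence when the counted period starts, and so its length, in one arm.

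**Working it through.** **1. The plan's sample size.** Inputs from Sample size and power calculation: 13.1% versus 6.4%, two-sided 5%, 80% power, 35.8% loss.

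n = [1.960·√(2·p̄·(1−p̄)) + 0.842·√(p1(1−p1) + p2(1−p2))]² / (p1−p2)², with p̄ = 0.0975

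= (0.822 + 0.351)² / 0.067² = 1.376 / 0.004489 ≈ 307 per arm, against the stated 309. For loss, 309 / 0.642 = 481.3, against the stated 481. The plan's figures reproduce and are not in question.

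**2. Abstinence that can be observed, counting from the quit date.** Six months = 6 × 30.44 = 182.6 days. Months abstinent = (assessment day − quit day) / 30.44.

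| Quit day after enrolment | At 6 months (day 182.6) | Answered one week later (day 189.6) | At 30 weeks (day 210) |
|---|---|---|---|
| 0 | 6.0 | 6.2 | 6.9 |
| 7 | 5.8 | 6.0 | 6.7 |
| 14 | 5.5 | 5.8 | 6.4 |
| 21 | 5.3 | 5.5 | 6.2 |
| 30 | 5.0 | 5.2 | 5.9 |

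At the scheduled questionnaire only a quit on about the day of enrolment gives 6 months. With the reminder week, quits up to day 7 do. A 30-week assessment would cover quits up to day 210 − 182.6 ≈ 27.

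**3. Counting from enrolment or intervention initiation.** Even at one cigarette a day, a daily smoker has smoked six by day 6 and is beyond the top of the 1–5 answer category. Most daily smokers who quit later in the month would fail. An occasional smoker who stays within the allowance could still succeed.

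**4. Calendar.** Enrolment on 30 September 2023 reaches 6 months on 31 March 2024 and 30 weeks on 27 April 2024. Both fall after February 2024.

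**5. Power, as illustration only.** Let f be the share of assumed abstainers in each arm who can meet the definition. The documents give no f, so the values are assumptions. With n = 500 per arm:

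power = Φ{[|p1−p2|·√n − 1.960·√(2·p̄·(1−p̄))] / √(p1(1−p1) + p2(1−p2))}

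| f | Rates as stated × f | Power | Rates × 0.642 × f | Power |
|---|---|---|---|---|
| 1 | 13.1% vs 6.4% | 95% | 8.41% vs 4.11% | 80% |
| 1/2 | 6.55% vs 3.2% | 69% | 4.21% vs 2.05% | 50% |
| 1/4 | 3.28% vs 1.6% | 40% | 2.10% vs 1.03% | 28% |

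The right-hand set applies if the planning rates exclude losses, since Statistical analysis counts participants lost to follow-up as smokers. The article does not say whether they do.

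**The case against.** Several stronger readings are tempting, and the document does not support them.

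- *The arms run on different clocks.* A reader might infer this from the quit-date step in the app. But questionnaires are timed from enrolment in both groups, and both arms receive their material after randomisation. What is open is the start of the abstinence period, in both arms alike.
- *Only the app prompts a quit date.* The control manual includes instruction on quitting and also goes to the app arm, but its text is not shown. A start date that differs by arm is a risk, not a stated fact.
- *Enrolment and intervention initiation conflict.* The two are close in time and no gap is described. In context, the sentence explains why follow-up is not tied to a target quit date. This is loose wording more than a contradiction.
- *Participants are promised a month to quit, or 30 weeks means 4 plus 26.* The month is an eligibility intention, and the article gives no derivation of the 30 weeks.
- *Late quitters will be scored as 6-month abstainers.* The article does not say so.
- *3-month abstinence is unworkable throughout.* The sentence groups five outcomes with three time points, and Table 1, which is not shown, may restrict them. At 6 months, anyone who quit by month 3 can meet it. What remains is that the sentence as worded includes the 1-month assessment, where 3 months cannot be observed.

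None of this touches the date arithmetic. Nor is it only a matter of condensation: the article itself states the 6-month schedule, the quit-date anchor and the 30-week follow-up.

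**Conclusion.** The point stands and should be settled before data collection. As written, 6-month abstinence from the quit date cannot be observed for participants who quit after about the day of enrolment (about day 7 with the reminder week). The shortfall is up to about one month for quits within the eligibility month and more for later ones. Moving the start to enrolment or intervention initiation does not rescue the endpoint for most daily smokers. The abstinence start date is not fixed in either arm, and the 30-week and 6-month statements do not agree.

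This rests only on the document's own dates and on participants quitting after they enrol. The power figures are weaker: they depend on an assumed f and on an unstated property of the planning rates. They show that the loss could be material, not how large it will be.

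**What to change.** Reconcile Study setting, Follow-up and data collection, Primary outcome and measures, and Secondary outcomes and measures.

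1. Use one abstinence start date for both arms, counted from randomisation, for example randomisation plus the 1-month eligibility window. Insert that calendar date in the question. Do not use individual quit dates or intervention initiation as anchors.
2. Then choose one of two options:
   - Place the final questionnaire at 30 weeks. With the start at day 28, this gives 210 − 28 = 182 days, or 26 weeks. With a full calendar month, about 213 days (7 months) would be needed.
   - Keep the 6-month questionnaire and name the endpoint abstinence from month 1 to month 6.
3. Assess 3-month continuous abstinence on the same basis, and not at 1 month.

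Neither option needs more participants. The first moves the last online questionnaire by about 4 weeks. The second is mainly wording, but the endpoint is then about 5 months, and the plan should say why rates given for 6-month abstinence still apply. The February 2024 completion date needs correcting in either case if recruitment runs to the end of September 2023: the last assessment falls at the end of March 2024, or on 27 April 2024 with 30 weeks.

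### Six-month continuous abstinence is scored from one recall question with no fixed start date, and the stated measurement makes no use of the same person's month-1 and month-3 smoking reports

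*Protocol article*

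**What the plan says.** The Abstract (Methods) states: "The primary outcome is self-reported 6-month continuous abstinence". Under Primary outcome and measures, the outcome follows the Russell 6 Standard without biochemical verification, with the gloss "tolerate fewer than five incidents of smoking from the quit date". The measurement is then fixed: it "will be measured through the question “Have you smoked at all since (date of the start of the continuous abstinence period", with the options "A: No, not a puff; B: 1–5 cigarettes; C: More than 5 cigarettes". No other source of information is named for this outcome. The same section says that "the follow-up in this study will be tied to the date of intervention initiation".

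Questionnaires go out "1 month, 3 months, and 6 months after enrollment" (Follow-up and data collection). Under Secondary outcomes and measures, 7-day abstinence is assessed at all three times, "The number of cigarettes smoked per day and the number of quitting attempts will be asked at each follow-up", and "The measurement of 3-month continuous abstinence is identical to that of 6-month continued abstinence as explained before". Statistical analysis compares self-reported continuous abstinence at each follow-up point. Relapse at a follow-up point is mentioned only in order to define secondary outcomes.

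**The concern.** The outcome claims abstinence over months, but a person's status comes from one retrospective answer. Two things in the text leave room for error.

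First, the period that the question covers is not pinned down. The definition counts from the quit date and the follow-up clock counts from intervention initiation. Nothing says which date goes into the question, or what happens to that date if a participant relapses and makes a new attempt. The protocol expects several attempts per person, because it counts them at each follow-up.

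Second, the trial already holds information that would expose many such cases, and the stated measurement does not use it. Take a participant who reports daily smoking at month 3, quits again at month 4, and at month 6 answers that not a puff has been smoked. On the measurement as written this is a success, although the month-3 record shows otherwise.

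At stake is whether the primary result describes sustained abstinence or a mixture of sustained and recent abstinence. Participants are not blinded and there is no biochemical check, so their own earlier answers are one of the few controls on the final answer. With an expected control rate of only 6.4%, a small number of misclassified people is a sizeable share of the successes.

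**Working it through.** **Plan's own figure.** Inputs from Sample size and power calculation: 13.1% versus 6.4%, two-sided 5%, power 80%, loss 35.8%. The pooled-variance formula

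n = [1.96·√(2p̄(1−p̄)) + 0.842·√(p1(1−p1)+p2(1−p2))]² / (p1−p2)², with p̄ = 0.0975,

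gives 307 per arm against 309 stated, and 309/(1−0.358) = 481.3 against 481 stated. Both reproduce, so the sample size contains no error that bears on this point.

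**Power at the planned 500 per arm.** Power = Φ[(d − 1.96·SE0)/SE1], where SE0 = √(2p̄(1−p̄)/n) and SE1 = √([p1(1−p1)+p2(1−p2)]/n). With d = 0.067, SE0 = 0.01876 and SE1 = 0.01864, this is Φ(1.62) = 94.8%. It takes the planned rates as holding for all 500 randomised per arm.

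**Effect of wrongly counted successes in both arms.** The documents give no rate, so 1, 2 and 3 percentage points (5, 10 and 15 people per arm) are an assumed range.

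| Added to each arm | APP vs control | Ratio | Power, n = 500 |
|---|---|---|---|
| 0 | 13.1% vs 6.4% | 2.05 | 94.8% |
| 1 point | 14.1% vs 7.4% | 1.91 | 92.9% |
| 2 points | 15.1% vs 8.4% | 1.80 | 90.9% |
| 3 points | 16.1% vs 9.4% | 1.71 | 88.9% |

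The absolute difference stays at 6.7 points by construction; the ratio and the precision suffer. At 2 points, 2/8.4 = 24% of counted control abstainers and 2/15.1 = 13% of counted APP abstainers would be false.

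If instead an equal share of true non-abstainers is wrongly counted, 2% gives 14.8% vs 8.3% (ratio 1.79, power 90%) and 5% gives 17.4% vs 11.1% (ratio 1.57, power 82%).

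**Worst-case illustration, all error in the APP arm.** With no true effect (6.4% in both arms) and 1, 2 or 3 extra points in the APP arm only (7.4%, 8.4%, 9.4%), the same formula gives a significant result favouring the APP in 9.1%, 22.6% or 42.0% of trials, against 2.5% nominal. This shows how sensitive a low-rate endpoint is. It does not predict what will happen.

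**Routes to misclassification.** (a) Fixed start date, truthful answer: a person who smoked daily at month 3 must choose the option for more than five cigarettes and is not a success. (b) Fixed start date, recall error: may be a false success. (c) Start date moved to a later attempt, by the participant or by how the blank is filled: a truthful answer gives a false success. The text excludes neither (b) nor (c).

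**The case against.** **The definition already excludes relapsers.** This is true for a truthful answer from a fixed date, as route (a) shows. What stands against it is that the date is not fixed and that recall can fail.

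**A cross-visit rule may exist elsewhere.** A reader might infer that the trial ignores the month-1 and month-3 reports. The documents do not say so. They say neither that these reports override the month-6 answer nor that they are set aside, and a full protocol or analysis plan, not shown, may deal with discordant answers. What can be said is narrower: the article chose to state how its primary outcome is measured, and that statement names one question and no check.

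**Bias towards the APP is speculative.** A reader might also infer that the error would favour the APP, because only its users are prompted to set a quit date in the app. No passage supports that direction. A recorded quit date could equally sharpen recall, the control manual also gives instruction on quitting, compensation is equal and independent of the answers, and outcome assessors are blinded. The one-arm figures should therefore not be read as an expected false-positive rate.

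**Interim answers are self-reports too.** This stands. They are unverified, and only people who returned an interim questionnaire can be contradicted, so unequal interim response between arms could add a small asymmetry of its own. They were, however, given closer to the events than the month-6 answer.

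**Self-report is an acknowledged limitation.** It is, in the Discussion, but with regard to biochemical verification. That does not address consistency with data the trial already holds.

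**Conclusion.** The point holds in a limited form. The primary outcome is measured by a single recall question whose start date is not fixed, and the stated measurement leaves unused the earlier reports that could contradict it. Some participants who relapsed and quit again could be counted as continuous abstainers. How many is unknown. Under an assumed 1–3 points in both arms of 500, the ratio falls from 2.05 to 1.91–1.71 and power from 95% to 93%–89%, still above the planned 80%. The conclusion does not depend on any difference between arms in how people answer. It is an inexpensive improvement to the endpoint definition that should be made, and no evidence that the trial's result will be invalid.

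**What to change.** 1. **Fix the start date first.** State one rule for the start of the abstinence period, including any grace period after enrollment, apply it identically in both arms, print the resulting date in the question, and say that a later attempt does not reset it. Without this the next step cannot be applied uniformly.
2. **Add a consistency condition.** Count a participant as a primary success only if the month-6 answer qualifies and no available month-1 or month-3 report relating to the time after the start date shows smoking beyond the allowed limit. A positive 7-day answer alone need not exceed that limit; the continuous-abstinence item and cigarettes per day are the more direct evidence. Smoking before the start date is no contradiction.
3. **Missed interim questionnaires.** These do not by themselves disqualify.
4. **Reporting.** Give the month-6-answer-only version as a sensitivity analysis, with interim response rates by arm.

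The allowed limit must be stated for step 2. The text tolerates fewer than five incidents while the middle answer option covers one to five cigarettes, and these should be reconciled at the same time.

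The cost is a few sentences in the outcome definition and a derivation from data already planned, with no extra questionnaire or visit. Abstinence rates may be slightly lower in both arms, and the check reaches only interim responders.
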